#### Strategies to improve adherence to interventions {11c}

The study participants are recommended to follow the study protocol. Given the nature of the trial, deviations from protocol regarding intervention are unlikely to occur. Included participants refusing allocated treatment, and crossovers, will remain in the trial and be included in the intention-to-treat analysis, unless explicitly denied.

#### Relevant concomitant care permitted or prohibited during the trial {11d}

Any medication necessary for anesthesia or the performance of either procedure is allowed, as well as any other medication prescribed to the participant. There are no restrictions on medication or any other treatment for participants in the trial.

#### Provisions for post-trial care {30}

The participants in Sweden are covered by the public patient insurance (Patientförsäkringen) as the study is carried out within the framework of public health care.

#### Outcomes {12}

Primary outcome measure:

The primary outcome is the difference in reoperation frequency within 3 months between the two groups. Reoperation is defined as any operative (surgical or endovascular) treatment regarding cSDH on the previously treated side(s).

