**Methods:**

The trial is academically driven and funded within existing public healthcare systems and infrastructure. Patients with uni- or bilateral cSDH, presenting with mild-to moderate symptoms, and admitted to neurosurgery on clinical grounds will be offered participation. Subjects are randomized 1:1 between conventional neurosurgical treatment (control) and endovascular embolization of the middle meningeal artery (intervention). Primary endpoint is reoperation due to clinically and/or radiologically significant recurrence within 3 months. Secondary endpoints include safety, technical success rate, neurological disability, and quality of life.

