### Trial design {8}

The SWEMMA trial is designed as a randomized, controlled, open, national, multicenter superiority trial with two parallel groups and a primary endpoint of reoperation within 3 months following either procedure. Clinical secondary outcomes assessments at 3 months and 12 months will be blinded. Randomization will be performed in blocks with 1:1 allocation.

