#### Intervention description {11a}

##### Intervention

Physicians performing the intervention are neuroradiologists with several years of experience in the endovascular field. The procedure is performed under sterile conditions in the angio suite, most commonly under conscious sedation.

Using standard endovascular techniques, arterial access is achieved in the femoral or radial artery. A guiding catheter is advanced to the common (CCA) and external (ECA) carotid arteries of the affected side(s) for baseline angiographic controls and anatomical delineation. A microcatheter is then used for super selective controls of the middle meningeal artery (MMA) for detailed anatomical delineation and then further advanced to a wedged treatment position in an appropriate MMA branch. In preparation, an intra-arterial vasodilating agent, a small dose of local anesthetic, and lastly DMSO are infused in the microcatheter. Under fluoroscopic control, the vessel is embolized with liquid embolysate (Onyx™ or Squid™ or Phil™) until no antegrade flow can be visualized. The process is repeated depending on the number of MMA branches to be treated. Post treatment control angiograms are performed in the ECA and CCA, and arterial access site is closed. An NCCT is performed in the angiolab, and the patient is transferred to neurointensive care unit (NICU) for postoperative controls. Estimated time from vascular access to closure is approximately 1–2 h depending on number of branches and sides to be treated.

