##### Control

Neurosurgical hematoma evacuation is a clinical routine treatment performed under sterile conditions in the operating theatre for cSDH. Most commonly, the procedure is performed under local anesthesia and conscious sedation. Depending on patient cooperability, general anesthesia may be indicated. In case of bilateral hematomas in need of simultaneous evacuation, the procedure is performed under general anesthesia. Antibiotic prophylaxis is given preoperatively.

Hair is removed, and a skin incision is made over the parietal or frontal bone (most often), and 1–3 burr holes are made in the skull and conjoined to form a minicraniotomy. The dura is coagulated and incised. The hematoma membrane is punctured when necessary and the hematoma irrigated using a catheter and fluid at room temperature. After evacuation, a small catheter is left in either the subdural space or under the galea, connected to a uribag for either closed, passive (subdural), or active (subgaleal) drainage. The head is slightly elevated, and the cavity is filled with fluid. Subcutaneous sutures secure the galea and subcutis and staples or sutures close the skin incision.

The patient is transferred to the NICU for 4 h of postoperative controls, or possibly overnight, if necessary. Estimated time from skin incision to wound closure is 30 min–1 h. Drainage is left in place for 24 h and then removed. Skin staples are removed after 7–14 days.

In cases of bilateral hematomas, the most expansive side is usually treated first, and the patient is followed clinically and radiologically to ascertain whether contralateral treatment is needed.

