#### Criteria for discontinuing or modifying allocated interventions {11b}

Post recruitment violation of inclusion and/or exclusion criteria are grounds for termination from the study. Unfavorable vascular anatomy are grounds for crossing over. Dropouts or crossovers will receive standard treatment as indicated by their clinical status and their data is retained unless explicitly denied.

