### Data collection and management

#### Plans for assessment and collection of outcomes {18a}

##### Primary outcome

The diagnosis of cSDH will be made on current imaging and clinical status of the included subject at the time of admittance to the recruiting neurosurgery department. Relevant clinical, radiological, and procedural data will be manually transferred from the participant medical records to the electronic case report form (eCRF). Data on reoperation (Swedish National Board of Health and Welfare Statistics Database) and date of death and primary cause of death (National Cause of Death Registry) will be collected at 3 months and 1 year post procedure. This data will be transferred to the eCRF. Participant medical records will be used to double-check the validity of the register data.

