## Discussion

The hypothesis of this trial is that endovascular treatment alone is safe and effective with a reduced reoperation rate compared to surgical evacuation in cSDH patients with clinical indication for surgical treatment.

The rationale for the trial design is the encouraging results with reduced reoperation rate for patients treated by endovascular embolization alone, where the reoperation rates are similar to those seen for endovascular treatment adjuvant to surgical evacuation. However, when routinely using endovascular treatment as an adjunctive, the increased complication rate by having two separate procedures may potentially outweigh any benefit of the combined treatments.

A minimally invasive treatment with reduced recurrence risk and comparable complication rates has however the potential for paradigm shift in the treatment of cSDH. Not within the scope of this trial, but eMMA has also been associated with a reduction in healthcare costs, the primary driver being fewer treatments needed [20]. A drawback of the endovascular treatment is that resolution of the hematoma is slower than prompt neurosurgical evacuation. Limited data on timing of clinical improvement with upfront eMMA is currently available. In our experience, a delay of clinical and radiological improvement of 5–10 days and 4–6 weeks respectively can be expected.

Internationally, treatment strategies for bilateral cSDH varies significantly, and reoperation rates for this group seem to be somewhat higher than unilateral cSDH, either by ipsilateral recurrence or opportunistic expansion of the unoperated side [21]. For bilateral cSDH randomized to neurosurgery and unilaterally evacuated at index procedure, additional analysis including subsequent operative treatment on the contralateral side will be performed.

When designing this trial, we have striven to follow clinical routine care as much as possible to facilitate transferal into clinical routine care, should the results be positive.

The trial is academically driven and locally funded by the collaborating efforts of the Neurosurgery and Interventional Neuroradiology departments at Skåne University Hospital. Sponsor is Region Skåne, the publicly funded healthcare provider for the south region of Sweden.

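### The primary event counts only operations on already treated sides, so never-embolised eMMA patients and bilateral patients can be counted differently by arm, and the planned additional analysis only partly repairs this

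*Protocol article*

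**What the plan says.** Outcomes {12} defines the event by side: "Reoperation is defined as any operative (surgical or endovascular) treatment regarding cSDH on the previously treated side(s". Trial design {8} sets "a primary endpoint of reoperation within 3 months following either procedure", and under Plans for assessment and collection of outcomes {18a} the reoperation data "will be collected at 3 months and 1 year post procedure". The clock therefore starts at the procedure, not at randomisation.

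Bilateral haematomas are eligible. For control, the Control section says that in bilateral cases "the most expansive side is usually treated first, and the patient is followed clinically and radiologically to ascertain whether contralateral treatment is needed"; it also provides for simultaneous evacuation of both sides. For eMMA, the Intervention section describes catheterising the "carotid arteries of the affected side(s" in one procedure.

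On non-adherence, section {11b} says: "Unfavorable vascular anatomy are grounds for crossing over". Such patients then receive standard treatment according to clinical status, and section {6b} names evacuation as the standard of care. Sections {11c} and {18b} keep crossovers and patients who refuse their allocation in the intention-to-treat analysis.

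The Discussion recognises part of the problem: "For bilateral cSDH randomized to neurosurgery and unilaterally evacuated at index procedure, additional analysis including subsequent operative treatment on the contralateral side" is to be performed. It is additional to the primary analysis and names only patients randomised to neurosurgery.

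**The concern.** The trial asks whether eMMA alone can replace evacuation. A patient allocated to eMMA who cannot be embolised and is evacuated instead is a case where that strategy did not avoid surgery. Yet no side has been treated when that evacuation takes place, so under the written definition it is not a reoperation. The patient contributes a non-event to the eMMA arm unless a second operation follows.

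In bilateral disease the definition follows whichever sides were treated at the index procedure, and the two arms differ systematically in that. The same clinical course, an operation on the second side some weeks later, can be an event in one arm and not in the other.

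The protocol states this definition outright, so this is not a detail left to an analysis plan. At stake is whether the between-arm difference in the primary outcome partly reflects the counting rule.

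**Working it through.** **Reproducing the plan's figure.** Inputs from Sample size {14}: 17% control, 6.5% eMMA, two-sided alpha 0.05, power 80%, likelihood ratio test, 144 per arm. With mean proportion (0.17 + 0.065)/2 = 0.1175 and KL the Kullback-Leibler divergence between two Bernoulli proportions:

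n per arm = (1.960 + 0.842)² / {2[KL(0.17, 0.1175) + KL(0.065, 0.1175)]} = 143.06, rounded up to 144.

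Enumerating all outcomes of the likelihood ratio test at 144 per arm gives power 80.9%. The plan's arithmetic reproduces; the issue is the event definition.

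**(a) Never-embolised eMMA patients.** Let x be the share of the eMMA arm never embolised and evacuated. The protocol gives no value for x. Assume 6.5% reoperation among the embolised and 17% after evacuation.

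- First evacuation not counted (as written): rate = (1 − x) × 6.5% + x × 17%.
- First evacuation counted as failure: rate = (1 − x) × 6.5% + x × 100%.

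| x | Patients of 144 | Not counted | Power | Counted | Power |
|---|---|---|---|---|---|
| 2% | 2.9 | 6.37 + 0.34 = 6.7% | 79% | 6.37 + 2 = 8.4% | about 61% |
| 5% | 7.2 | 6.175 + 0.85 = 7.0% | 76% | 6.175 + 5 = 11.2% | 30% |

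At x = 5%, the difference from 17% is 10.0 points as written and 5.8 points if these evacuations count. The right-hand powers describe the stricter contrast, not the planned primary analysis.

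**(b) Bilateral patients.** Setting the sections side by side, does a later operation on the second side count?

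| Sides treated at index | Primary outcome | Discussion analysis |
|---|---|---|
| Control, one side | no | yes |
| Control, both sides | yes | yes |
| eMMA, both sides | yes | yes |
| eMMA, one side | no | no |

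The primary outcome is uneven when one-side controls are compared with both-side eMMA patients, and the Discussion analysis levels that. It becomes uneven itself when one-side controls are compared with one-side eMMA patients, because it adds the second side for neurosurgery only.

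To illustrate the primary count, assume a bilateral share b, a 17% risk per treated side in both arms, independent sides, control treated on one side and eMMA on both. Control is counted at 17.0%. eMMA is counted at (1 − b) × 17% + b × (1 − 0.83²), where 1 − 0.83² = 31.11%:

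- b = 10%: 15.30 + 3.11 = 18.4%
- b = 20%: 13.60 + 6.22 = 19.8%
- b = 30%: 11.90 + 9.33 = 21.2%

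Thus 1.4 to 4.2 points against eMMA would arise with no true difference per side. The bilateral share, the per-side risk and the independence are all assumptions.

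**The case against.** Not calling the first treatment of an untreated side a reoperation is a defensible choice, and the protocol discloses the contralateral issue. The bilateral asymmetry works against eMMA, so in a superiority trial it costs power and does not by itself produce a false positive. Counting a single evacuation as failure in one arm but not the other would also be unequal, since evacuation is the allocated treatment in control. All of this stands, and it is why the primary definition need not be rewritten. It does not answer the never-embolised case, where the literal rule favours eMMA and no section counts the evacuation otherwise. Technical success as a secondary outcome and the planned per-protocol analysis do not do so either.

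A reader might infer more than the protocol supports:

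- That the Discussion analysis merely swaps one one-sided count for another, in eMMA's favour. Where eMMA embolised both sides, it equalises the count.
- That the control rate is overstated and power falls to 66% or 57% (control rates of 15% or 14%). That requires the 17% to include contralateral operations. Section {14} bases it on excess operations per patient and a cited report, and does not say whether they are included.
- That the abstract sets a competing definition: "Primary endpoint is reoperation due to clinically and/or radiologically significant recurrence within 3 months". It is a summary; the operative definition is in Outcomes {12}, and neither the primary objective nor Trial design {8} adds a recurrence condition. Aligning the wording would be a minor tidy-up.
- That the late clock hides many deteriorations before embolisation. The protocol describes none, and its timeline puts randomisation and treatment in the same week.
- That the net bias could never be known. Procedural data go into the eCRF and reoperations are checked against medical records, so events can be recounted under another rule.

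**Conclusion.** The concern holds in limited form and should be fixed. For unilateral patients who receive their allocated procedure, the same operations count in both arms. The unevenness is confined to eMMA-allocated patients never embolised, where it favours eMMA, and to bilateral patients, where it can work against eMMA. The net direction cannot be read from the protocol, which gives neither a crossover rate nor a bilateral share. The figures above (eMMA 6.7% to 7.0% against 8.4% to 11.2% for 2% to 5% never embolised and evacuated) show only that about three to seven patients could matter against a planned difference of 10.5 points. They assume that all such patients are evacuated and that the planning rates apply. The reading is clear where embolisation was never attempted; for an attempted but failed embolisation, the text does not say whether the side becomes a treated one. The protocol does not support the stronger conclusion that the primary contrast is already compromised.

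**What to change.** Keep the primary definition and make three changes before outcomes are examined by arm.

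1. Run the Discussion's contralateral analysis by one patient-level rule in both arms: any later cSDH operation on any side with cSDH at baseline counts. Report intended second-stage evacuations separately, so that staged treatment in control is not presented as failure.
2. Pre-specify an intention-to-treat sensitivity analysis, timed from randomisation in both arms, that counts as failure any evacuation in an eMMA-allocated patient who was not embolised. It needs its own rule: counting operations after the index procedure would miss a crossover's first evacuation, because that evacuation is the index procedure.
3. State whether an attempted but failed embolisation makes a side previously treated for the purpose of the primary outcome.

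The cost is some wording and two extra analyses on data already collected. The second may be less favourable to eMMA than the primary analysis. Redefining the primary event itself is a debatable trade-off and is not needed for this repair.

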#### Secondary outcome measures:

I.Difference in neurologic disability, assessed by modified Rankin Scale (mRS), between groups at 3 and 12 monthsII.Difference in quality of life, assessed by EuroQoL 5D (EQ-5D) between groups at 3 and 12 monthsIII.Difference in residual hematoma volume (mL) between groups, assessed by NCCT of the head at 3 months post treatmentIV.Technical success rate of endovascular treatment (percentage of interventions), defined as post procedurally no visualization of antegrade flow in branches of the MMA distal to non-target arterial branches, i.e., arteries to the orbit or cranial nerves, on final angiogramV.All complication rates; number and severity of adverse and serious adverse events between groups.VI.Composite endpoint: difference in death or reoperation frequency within 3 and 12 months after treatment between groups

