#### Secondary variable analyses

Binary secondary outcomes (i.e., technical success rate, all complications rate, and composite outcome of death and re-operation within 3 months) will be analyzed using logistic regression models (as described for the primary outcome). Kaplan–Meier time-to-event analysis with follow-up time as the time scale will also be used to assess the impact of intervention on the composite outcome of death and re-operation with differences between survival curves assessed using the likelihood ratio test. Ordinal secondary outcomes (i.e., mRS and EQ5D) will be assessed at 3 and 12 months after treatment. To assess the effect of intervention at each time point, ordinal logistic regression models will be used. For the continuous secondary outcome (i.e., hematoma volume), a generalized linear model will be used. All analyses will account for enrolment center and baseline characteristics unevenly distributed between study arms when applicable.

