### Adverse event reporting and harms {22}

#### Adverse events and complications

Throughout the course of the clinical investigation, all adverse events will be recorded on the applicable adverse event form in the eCRF and in the subject’s medical records. In this study, adverse events will be defined and classified per ISO 14155:2020(E) Clinical Investigations of Medical Devices in Human Subjects—Good Clinical Practice and as further described in this protocol. The date of onset, date of resolution, severity, and action taken will be evaluated by the Investigator. The relationship to the device, relationship to the procedure, and clinical significance will be evaluated. The neurological outcomes and adverse events will be reported.

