#### Adverse event classification and definitions

An adverse event (AE) is any untoward medical occurrence, unintended disease, or injury, or untoward clinical signs (including abnormal laboratory findings) in subjects, users, or other persons, whether or not related to the medical device (ISO 14155:2011).

Note 1: This definition includes events related to the medical device or the comparator.

Note 2: This definition includes events related to the procedures involved.

Note 3: For users or other persons, this definition is restricted to events related to medical devices.

Disease signs and symptoms that existed prior to study participation are not considered AEs unless the condition recurs after the subject has recovered from pre-existing condition or the condition worsens in intensity or frequency during the study.

A serious adverse event (SAE), as per the European Standard ISO 14155:2020(E), is an AE that led to any of the following:▪ Death▪ Serious deterioration in the health of subject, users or other persons as defined by one or more of the following:

A life-threatening illness or injuryA permanent impairment of a body structure or body function including chronic diseasesIn-patient or prolonged hospitalizationMedical or surgical intervention to prevent life-threatening illness of injuryFetal distress, fetal death, a congenital abnormality, or birth defect including physical or mental impairment

Planned hospitalization for a pre-existing condition, or a procedure required by the protocol, without serious deterioration in health, is not considered a serious adverse event.

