#### Adverse event assessments

Relatedness:Procedure-related: Event has a strong temporal relationship to the study procedure. This includes AEs attributable to any device(s) used at procedure, such as access devices, delivery microcatheters, embolic materiel, non-ionic contrast media, guidewires, or any other adjunctive, approved/cleared device for treatment of intracranial vascular pathologyDevice-related: Event has a strong temporal relationship to the use of any other particular device(s)Unknown: Event relationship cannot be attributed to any of the above categories and remains undetermined

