#### Procedure-related adverse events

An adverse event is procedure-related when, in the judgment of the investigator; it is reasonable to believe that the event occurs during the interventional or standard procedure, irrespective of devices used.

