#### Event reporting requirements

Any adverse event that occurs during the study must be recorded and reported using the appropriate adverse event eCRF and recorded in the subject’s medical records.

These will include events occurring from the point of consent until a subject exits the study. The investigator must sign each AE eCRF report. Investigators must obtain all information available to determine the causality and outcome of the AE and to assess whether it meets the criteria for classification as serious and the relationship of each adverse event to the procedure or device. This determines whether it requires notification to the sponsor, regulatory agency, and, as applicable, EC, within the specified reporting timeframe. AEs will be categorized using the definitions in Sects. 18.1–18.5.

Pre-existing medical conditions or symptoms occurring prior to the start of the procedure should not be reported as adverse events. In the situation where there is a worsening of a pre-existing medical condition or symptom due to a study related procedure, an adverse event should be reported.

In the case of any AE, the investigator shall submit to Sponsor a report within 10 working days after the investigator first learns of the event.

The investigator is required to report all SAEs within 24 h after first learning of the event to the sponsor. The primary method of reporting SAEs will be through the eCRFs. If the database is unavailable, the investigator may fax or email in the information. As soon as the database becomes available, the investigator must complete data entry. Depending upon the nature and seriousness of the adverse event, the sponsor may request the investigator to provide anonymous copies of the subject’s available supporting documentation (such as the subject’s laboratory tests, hospital records, discharge reports, autopsy reports, investigator summaries, etc.) to document the adverse event. The sponsor is responsible in Europe for ensuring that the required and adequate information concerning the reported SAE is relayed to the appropriate Ethics Committee and Competent Authority using the MEDDEV 2.7/3 SAE Report Table. All other adverse events (i.e., other than serious adverse events) must be recorded on the appropriate adverse event eCRF.

The sponsor, in cooperation with the Investigator, will assess all serious adverse events for potentially reporting to the Regulatory Authorities and EC.

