#### Data Safety Monitoring Board

The Data Safety Monitoring Board (DSMB) comprises at least 3 non-Investigator clinicians with expertise in interventional neuroradiology/neurosurgery that will review all adverse events occurring in the study according to the DSMB Charter. The DSMB will meet and review all clinical events continuously.

Any event meeting the definition of serious adverse event (SAE) must be adjudicated by the DSMB. The DSMB will also be provided with listings of all events and may choose to adjudicate events that are not serious in nature. Members may discuss any event with the investigator who was involved with the subject in question. The DSMB will use the same rating scale for relatedness. The DSMB adjudicated adverse events will be used in the analysis of the primary safety endpoint; DSMB will review and adjudicate the Medical Monitor’s categorization of event type and severity using the rating system previously referenced.

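### The safety outcome promises number and severity of adverse events, but the only analysis named for it is a yes/no complication rate that uses neither

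*Protocol article*

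**What the plan says.** The secondary objectives in the protocol article include a comparison of how many complications occur in each arm and how severe they are. Outcome V, under Secondary outcome measures, is "All complication rates; number and severity of adverse and serious adverse events between groups".

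Secondary variable analyses sorts the secondary outcomes by type. It begins: "Binary secondary outcomes (i.e., technical success rate, all complications rate, and composite outcome of death and re-operation within 3 months", and assigns these to logistic regression. The ordinal outcomes are given as mRS and EQ-5D, and the continuous outcome as hematoma volume. Event count and event severity appear in none of the three groups.

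On what is recorded, Adverse event classification and definitions says: "An adverse event (AE) is any untoward medical occurrence, unintended disease, or injury, or untoward clinical signs (including abnormal laboratory findings", whether or not related to the device. Event reporting requirements sets the period: "These will include events occurring from the point of consent until a subject exits the study". Severity is captured: "The date of onset, date of resolution, severity, and action taken will be evaluated by the Investigator".

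On relatedness, Adverse event assessments calls an event procedure-related when it is closely linked in time to the procedure. Its remaining categories are device-related and "Unknown: Event relationship cannot be attributed to any of the above categories and remains undetermined". The section headed Procedure-related adverse events uses a different test: "it is reasonable to believe that the event occurs during the interventional or standard procedure, irrespective of devices used".

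The Data Safety Monitoring Board section states: "The DSMB adjudicated adverse events will be used in the analysis of the primary safety endpoint". The outcome list contains no endpoint of that name.

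**The concern.** The objective and the outcome ask how many events occurred and how bad they were. The named model asks only whether a patient had any. An analysis plan that follows the protocol would inherit this gap, and one that departs from it would contradict the protocol.

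The second worry is dilution. If the binary variable takes in every adverse event from consent to exit, then intercurrent illness over 12 months in patients aged up to 90 will mark many patients as having an event in both arms. A real procedural difference, in either direction, would then be hard to see. The Discussion rests the case for embolization on fewer recurrences with a similar complication burden, so a non-significant result on a diluted measure could be taken as reassurance.

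The relatedness coding does not offer a clean alternative. A complication that appears days after either procedure can meet one definition of procedure-related and fail the other, and an event clearly due to something else has no category except the undetermined one.

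**Working it through.** **1. Outcome against analysis.**

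| Quantity in the objective or outcome V | Analysis named in Secondary variable analyses |
|---|---|
| Complication rate | Logistic regression of a binary variable |
| Number of AEs and SAEs | None |
| Severity of AEs and SAEs | None |

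One of the three elements has a stated analysis. This step needs no assumption.

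**2. The plan's own figure.** The protocol gives no figure for the safety outcome. The only planned number used below is 144 per arm (Sample size), set for reoperation at 17% v 6.5%, two-sided alpha 0.05, power 80%. The unpooled normal formula gives n = (1.960 + 0.842)² × (0.17×0.83 + 0.065×0.935) / 0.105² = 7.849 × 0.2019 / 0.01103 = 143.7, so 144 per arm. The likelihood ratio test named in the protocol also gives 144, with power 80.3%. The figure reproduces.

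**3. Dilution, as an illustration.** From the documents: n = 144 per arm, and a significance level of 0.01 for secondary outcomes (Adjustment of significance levels and confidence intervals). Assumed: related-event rates s of 15% v 5%, and a background of unrelated events in a proportion b of patients, equal in both arms and independent of related events. Then

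P(any event) = 1 − (1 − s)(1 − b).

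The difference between arms is therefore (1 − b) × 10 points. Power is Φ[(d − 2.576 × SE₀)/SE₁], where d is the difference, SE₀ = √[2p̄(1 − p̄)/144] with p̄ the mean of the two rates, and SE₁ = √{[p₁(1 − p₁) + p₂(1 − p₂)]/144}.

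Worked line for b = 20%: the rates are 1 − 0.85×0.80 = 0.32 and 1 − 0.95×0.80 = 0.24. So d = 0.08, SE₀ = 0.0529, SE₁ = 0.0527, and (0.08 − 2.576×0.0529)/0.0527 = −1.07, giving power 14%.

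| Background b | Any-event rates | Power, 0.01 | Power, 0.05 |
|---|---|---|---|
| 0% | 15% v 5% | 60% | 81% |
| 10% | 23.5% v 14.5% | 26% | 49% |
| 20% | 32% v 24% | 14% | 33% |
| 30% | 40.5% v 33.5% | 9% | 23% |
| 50% | 57.5% v 52.5% | 4% | 13% |
| 70% | 74.5% v 71.5% | 2% | 8% |

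With a smaller assumed difference, 10% v 4%, power at 0.01 is 28% with no background and 5% with b = 20%.

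**4. Relatedness side by side.** Take a wound or access-site infection that appears after the procedure. Under Adverse event assessments it can be procedure-related, because closeness in time is the test. Under Procedure-related adverse events it is not, because it did not happen during the procedure. An unrelated illness months later fits neither the procedure nor the device category, and is left as undetermined.

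**The case against.** A reader might infer that the safety comparison is bound to saturate, and that the trial cannot tell a trivial event from a disabling one. The documents support neither reading.

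- The statistical section does not define the all-complications rate or its period. Treating it as every adverse event from consent to exit joins the outcome to a general definition and a reporting rule, both of which govern what is recorded. The text permits that reading but does not state it.
- No adverse event rate is given, so saturation is a forecast. The power figures rest on assumed rates, and even with no background the power is only 60%, so part of the weakness comes from the sample size and the 0.01 level.
- Disabling events are visible elsewhere. Severity is recorded, the DSMB must adjudicate every serious event, mRS is compared at 3 and 12 months, and death is part of composite outcome VI.
- Outcome V does list complication rates first, so the binary analysis answers one of its parts.

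All four points stand, and they limit the claim. It can also be said that counts, severity tables and event windows are usually left to an analysis plan, which is not shown. That would answer a protocol that is silent. This one names the type of variable and the model, in lists worded as complete, and the choice omits two of the three quantities it defined.

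A further objection concerns the remedy. Treatment is open, so a main safety comparison built on investigator-judged relatedness would invite attribution bias. That is right, and related events should be supportive only.

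**Conclusion.** The point holds as a mismatch between the outcome and its analysis. Number and severity are promised, and the only named model uses neither. This rests on the text alone.

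Dilution is conditional. If the binary variable does cover all adverse events to study exit, a modest background is enough to weaken it: under the assumed 15% v 5%, power at 0.01 falls from 60% to about 14% with a 20% background and about 4% with 50%. These figures show direction and rough scale. They assume independent background events, equal between arms, at rates the protocol does not give.

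The conflict between the two definitions of procedure-related, and the missing category for unrelated events, are separate faults on the face of the text. They do not enter the binary model, but they affect any analysis of related events.

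The fault is in the named analysis, not in the recording of severity. It concerns a secondary outcome and does not touch the primary comparison.

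**What to change.** In Secondary variable analyses, define the all-complications rate (which events, over what period) and keep it as one descriptive line. Add:

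- **Counts:** AEs and SAEs per patient by arm, with a negative binomial model, or a Poisson model with robust errors, and an offset for follow-up time.
- **Severity:** worst severity per patient, as an ordinal outcome.
- **Serious events:** the proportion of patients with at least one DSMB-adjudicated SAE.
- **Related events:** the proportion with a procedure- or device-related event within a fixed period after treatment, as a supportive comparison only, because attribution is unblinded.

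State which of these, if any, is tested at 0.01, and report the others as estimates with confidence intervals. In the DSMB section, either tie the primary safety endpoint to one of these measures or delete the term.

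Reconcile the two definitions of procedure-related into one that applies to both arms and covers delayed events, and add a category for events that are not related.

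Onset date, severity and relationship are already recorded, so no new assessments of patients are needed. The cost is a longer safety table, one added eCRF option and a minor protocol amendment. Because recruitment began in March 2022, events already coded would need to be reclassified under the single definition.
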